### Description of the LVOne test and biomarker assays

The LVOne is a single-use point-of-care test comprising two portable lateral flow assays: one for detecting D-dimer and the other for detecting GFAP. Each assay provides a semi-quantitative estimate of biomarker concentration based on test-line intensity. In each assay, a blood sample is mixed with an antibody-nanoparticle conjugate and applied to the sample port. Following the addition of a reaction buffer, the resulting complex moves along the membrane and binds to a capture antibody, producing a coloured test line whose visual intensity increases with biomarker concentration.

Test validity is determined by the presence of both GFAP and D-dimer control lines. Tests in which either control line is absent are classified as invalid. Test-line intensity for GFAP and D-dimer is scored on an ordinal 0–10 scale (0=no visible test line; 1–10=increasing band intensity), using the manufacturer’s reference card. The concentration ranges represented by the reference card are 213–30 000 pg/mL for GFAP and 400–15 000 ng/mL for D-dimer. A GFAP test-line intensity score of ≥1 corresponds to a concentration of ≥213 pg/mL, while a D-dimer test-line intensity score of ≥2 corresponds to a concentration of ≥600 ng/mL. In accordance with manufacturer-prespecified thresholds, GFAP is considered positive if any visible test line is present (intensity score ≥1) and negative if the intensity score is 0. D-dimer is considered positive if the test-line intensity score is ≥2, and negative if the intensity score is 0 or 1.

All LVOne tests will be interpreted at the point of care by a trained primary reader (Reader 1), who will record control line validity and intensity scores for each biomarker using a standardised procedure and reference card. Where available, a second independent reader, blinded to the primary reader, will also record control-line validity and intensity scores to allow assessment of inter-reader agreement.

Stroke subtype classification using the LVOne will be performed in accordance with the manufacturer’s LVOne intended use and the prespecified combined clinical-biomarker rule to classify patients into haemorrhagic stroke or LVO. Haemorrhagic stroke will be defined as FAST ≥1 and GFAP positive (intensity ≥1), irrespective of D-dimer. LVO will be defined as FAST ≥2, GFAP negative (intensity=0) and D-dimer positive (intensity ≥2). All other combinations will be classified as non-haemorrhagic and non-LVO. These LVOne stroke subtype classifications will not be performed by clinical staff in real time; instead, they will be derived analytically by the research team in the analysis phase at the end of the study based on the recorded FAST scores and LVOne intensity readings.

An enzyme-linked immunosorbent assay (ELISA) will also be used to quantify GFAP and D-dimer concentrations. Results from the ELISA will be compared with those from the lateral flow assays to assess analytical agreement. If GFAP and D-dimer alone are insufficient to distinguish stroke subtypes with adequate accuracy, additional plasma biomarkers previously shown to differentiate between stroke, stroke mimics, and specific subtypes may also be explored.

### Venous blood sample processing, analysis and storage

A 4-mL venous blood sample will be drawn into an acid citrate dextrose anticoagulant tube as soon as possible after hospital arrival and always within 6 hours of symptom onset. Samples will be stored at 4 °C and transported to the research laboratory, where plasma will be separated by centrifugation within 1 hour of collection, aliquoted and stored at −80 °C.

Plasma aliquots will be stored on site until transfer to the central laboratory (UpFront Diagnostics) for analysis of GFAP and D-dimer. Following study completion, any remaining samples will be stored for future ethically approved research, subject to specific additional consent from participants.

### End of study

The end of the study will be defined by the study end date, or the recruitment of at least 257 participants, including a minimum of 26 patients with ICH and 26 with LVO, whichever occurs first.

## Study participants

### Inclusion criteria

The patient arrived at the study hospital via emergency ambulance.The patient is 18 years of age or older.The ambulance staff suspected a new acute stroke prior to arrival at the hospital.Stroke symptoms began within 6 hours of research sample collection (if unwitnessed onset, patient was last known to be well within 6 hours).Blood samples can be collected prior to the administration of thrombolysis or any other acute treatment.Urgent brain imaging is planned in line with national stroke guidelines.

### Exclusion criteria

The patient was assessed at another hospital and transferred for ongoing care.The patient had a recent diagnosis (within the preceding 4 weeks) of deep vein thrombosis, pulmonary embolism, arterial embolism, stroke, transient ischaemic attack, long bone fracture, major trauma or surgery under general anaesthesia (which may increase D-dimer levels).The patient had a recent head injury (within the preceding 4 weeks) requiring hospital care (which may increase GFAP levels).Stroke symptoms started more than 6 hours prior to sample collection.

### Patients who withdraw consent

If a patient chooses to withdraw from the study, any data collected (LVOne test results, blood samples and clinical data) will be securely destroyed. However, as data will be anonymised as soon as possible following study completion, it will not be possible to remove information once anonymisation has occurred, since it will no longer be traceable to individual participants.

### Patient and public involvement

The DIAGNOSIS study was reviewed by the Geoffrey Jefferson Brain Research Centre Patient, Carer and Public Involvement group. Members supported the study’s aims and endorsed the deferred consent model given the time-critical nature of acute stroke care. Their feedback informed the approach to early sampling and consent process.

## Reference standard

The final in-hospital diagnosis of stroke subtype, as determined by stroke consultants or senior physicians responsible for the patient’s care, will serve as the reference standard. Diagnoses will be based on clinical assessment, brain imaging (CT and/or MRI), laboratory findings and other relevant examinations. Treating clinicians will be blinded to the LVOne test and research biomarker results. Where diagnostic uncertainty arises, the case will be reviewed and adjudicated by the site principal investigator, who is a senior stroke consultant. If the site principal investigator’s opinion differs from the clinical team’s diagnosis, a third independent senior stroke clinician will be asked to adjudicate.

For each participant, the final diagnosis will be recorded as IS, ICH or a stroke mimic, and in cases of IS, the presence of LVO will be recorded.

## Data collection, source data and confidentiality

For patients who provide consent, study data will be recorded on a case report form and entered into a secure study database hosted at the University of Manchester. Collected variables will include demographics (eg, age and sex), presenting symptoms (eg, unilateral weakness and speech disturbance), prehospital and admission vital signs (eg, blood pressure, heart rate and oxygen saturation), past medical history, and details of blood sampling and LVOne test line status.

From the ambulance patient report form, prehospital stroke scale assessments (eg, FAST) and their components (face weakness, arm weakness and speech disturbance) will be extracted, together with other presenting symptoms, including those typical of posterior circulation stroke (eg, vertigo, ataxia and visual disturbance).

Key time points, including symptom onset or last known well, first paramedic contact, hospital arrival, and LVOne and venous sampling will be recorded to calculate onset-to-sample and prehospital-to-sample intervals.

Data will be collected from the ambulance patient report form, as well as from assessments and records in the emergency department. During follow-up, additional information will be obtained, including final diagnosis, brain imaging findings and details of acute treatments.

All brain imaging performed during the acute admission will be pseudonymised and transferred to the DIAGNOSIS research team at the University of Manchester for further analysis. These scans will be used to confirm stroke subtype and to characterise lesion location, size and other imaging features relevant to clinical presentation and biomarker levels.

## Statistical considerations

### Statistical analysis

The statistical analysis plan will be finalised prior to analysis in collaboration with the lead study statistician. Multivariable regression will be used to develop diagnostic models based on the collected data, and other statistical or machine learning methods will be considered where appropriate.

The set of clinical predictors to be included in the models will be informed by prior literature and clinical plausibility and will not be selected solely on the basis of univariable associations. The number of candidate predictors will be guided by sample size criteria proposed by Riley *et al*^18
19^ to minimise overfitting and ensure reliable estimation in diagnostic prediction models.

Model development will follow best practices described by Steyerberg,^20^ incorporating internal validation via bootstrapping to estimate and adjust for optimism in model performance.

Model performance will be assessed in terms of discrimination (area under the receiver operating characteristic curve), calibration (using calibration plots and calibration slope and intercept) and clinical utility using decision curve analysis.^21^ Sensitivity, specificity and predictive values will also be reported with 95% CIs.

Model development and reporting will adhere to the Transparent Reporting of a Multivariable Prediction Model for Individual Prognosis or Diagnosis+Artificial Intelligence guidelines.^22^ Analyses of biomarkers performed separately will be reported in accordance with the Standards for Reporting of Diagnostic Accuracy Studies guidelines to ensure a transparent and complete evaluation of diagnostic accuracy.^23^ While we will lack the power to test for heterogeneity by subgroup, exploratory secondary analysis will be considered, including testing by onset-to-test time of 0–2 hours vs 2–6 hours.

### Missing data

Missing data in clinical variables and laboratory biomarker measurements may arise due to incomplete documentation or unsuccessful sample collection. Such data will be assessed and handled using appropriate statistical methods in line with best practice for prediction model development. Where appropriate, multiple imputation will be used under the assumption that data are missing at random. Participants with missing LVOne results will be excluded from the primary analysis. Sensitivity analyses will be conducted, where appropriate, to evaluate the potential impact of missing data on model development and performance.

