### Sample size

This study aims to ‘rule in’ patients with ICH and LVO; therefore, the sample size calculation prioritises high specificity.

Assuming a 10% prevalence of both ICH and LVO, a sample size of 257 patients with suspected stroke is required, including a minimum of 26 confirmed cases for each subtype. The sample size calculation is based on a diagnostic accuracy framework using the method described by Bujang and Adnan,^24^ in which null and alternative hypotheses are specified for sensitivity and specificity.

Based on our previous work, which demonstrated a specificity of 90% and a sensitivity of 50% for a clinical model with nine predictors,^25^ the current study is powered to detect an improvement to 95% specificity and 80% sensitivity for the detection of ICH and LVO, with 80% power and a significance level of 0.05.^24^

The number of cases contributing to the primary analysis will be monitored throughout the study. If necessary, recruitment may be adjusted to ensure adequate representation of target subtypes.

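### Participants without an LVOne result are dropped from the primary analysis, invalid tests are not tied to that rule, and the 257 carries no allowance for lost tests

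*Protocol article*

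**What the plan says.** All references are to the protocol article.

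- **Missing data.** Multiple imputation may be used for clinical variables and laboratory biomarkers. The index test is treated differently: "Participants with missing LVOne results will be excluded from the primary analysis". The section closes with "Sensitivity analyses will be conducted, where appropriate, to evaluate the potential impact of missing data on model development and performance".
- **Description of the LVOne test and biomarker assays.** LVOne consists of two strips, one per marker. "Tests in which either control line is absent are classified as invalid". The haemorrhage rule uses FAST and GFAP whatever the D-dimer reading; the LVO rule uses FAST and both markers. "All other combinations will be classified as non-haemorrhagic and non-LVO". ELISA values of the same two markers come from venous blood, which Study procedures says is drawn at the same time as the finger-prick.
- **Sample size.** "This study aims to ‘rule in’ patients with ICH and LVO", so specificity is given priority. "Assuming a 10% prevalence of both ICH and LVO, a sample size of 257 patients with suspected stroke is required". Each subtype must supply at least 26 of these patients. The null values come from earlier work that "demonstrated a specificity of 90% and a sensitivity of 50% for a clinical model with nine predictors"; the alternatives are 95% specificity and 80% sensitivity, at 80% power and a 0.05 significance level. Cases entering the primary analysis are counted as the study runs, and recruitment may be changed to secure enough of the target subtypes.
- **End of study.** The study ends at its end date or once at least 257 participants, with at least 26 ICH and 26 LVO, have been recruited, whichever is earlier.

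**The concern.** Three things follow from the exclusion rule as written.

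1. **The denominator.** A patient whose test fails cannot be ruled in by it. Accuracy among usable results answers how good the reading is when there is one. It does not answer how many ICH or LVO patients the test picks out among all those tested. The second question matters for later ambulance use, and Justification for hospital-based design presents this study as establishing feasibility and operational characteristics as well as accuracy.
2. **Invalid tests and usable data.** The text never links invalid to missing. If the two are the same, a failed D-dimer control line removes a valid GFAP score from the haemorrhage rule and from the GFAP-alone objective, neither of which needs D-dimer. Model development, the primary objective, loses these patients too, although ELISA values of the same markers could inform imputation.
3. **Power.** The calculation leaves no room for lost tests in the quantity that drives it, the number of non-cases.

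**Working it through.** **Inputs** (Sample size): specificity 0.90 against 0.95; sensitivity 0.50 against 0.80; prevalence 0.10 per subtype; power 0.80; alpha 0.05. Sidedness is not stated.

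**Step 1: reproduce 257.** One-sample exact binomial test with 0.025 in the upper tail.
- Specificity: the smallest number of non-cases with power of at least 80% is 231 (reject at 217 or more correct; power 81.6%).
- 231 / 0.90 = 256.7, so N = 257, of whom 26 are cases at 10% prevalence.
- Sensitivity: the smallest number of cases reaching 80% is 20, so specificity drives N. With 26 cases the power is 86.9%.
- Other variants miss 257: two-sided normal approximation 265, one-sided exact 199, one-sided normal 204.

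So 257 contains no inflation, and 231 is the first number of non-cases to reach 80% power.

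**Step 2: effect of the exclusion if recruitment stops at 257.** The loss rate is an assumption. Analysed N = 257 × (1 − m), rounded, with 10% of these as cases. True sensitivity and specificity among usable tests are kept at 80% and 95%.

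| Loss m | Analysed N | Non-cases | Specificity power, exact (normal approx.) | Cases | Sensitivity power, exact |
|---|---|---|---|---|---|
| 0% | 257 | 231 | 81.6% (78.5%) | 26 | 86.9% |
| 2% | 252 | 227 | 75.2% (77.6%) | 25 | 89.1% |
| 5% | 244 | 220 | 78.6% (76.0%) | 24 | 81.1% |
| 10% | 231 | 208 | 75.6% (72.9%) | 23 | 84.0% |

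Exact power is saw-toothed, which is why 2% looks worse than 5%. Exact power for specificity is below 80% at every n from 180 to 230.

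**Step 3: recruitment needed to keep 257 analysable,** 257 / (1 − m), rounded up: 263 at 2%, 271 at 5%, 286 at 10%.

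**Step 4: valid-only against all-tested accuracy.** If failures are unrelated to diagnosis and each is counted as not ruled in:
- sensitivity = 0.80 × (1 − m): 78.4%, 76.0%, 72.0% at 2%, 5%, 10%;
- specificity = 0.95 × (1 − m) + m: 95.1%, 95.25%, 95.5%.

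These differences come from changing the quantity estimated. They are not a bias in the valid-only figure.

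**The case against.** **Safeguards exist.** 257 is a minimum, cases in the primary analysis are monitored and recruitment may be adjusted. A reader might infer that the analysed sample will fall below the powered size; the documents do not support that, because the shortfall depends on an unstated loss rate and on recruitment not being extended. What remains is narrower: monitoring follows cases and target subtypes while non-cases set N, and the stopping rule counts people recruited and can be overtaken by the end date.

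**The exclusion need not bias anything.** A reader might infer that it overstates sensitivity. If results are lost independently of disease and marker level, valid-only accuracy is unbiased for the test when it works, and no mechanism for loss is documented. A fall from 80% to 72%, with power to beat 50% on 26 cases falling from 86.9% to 55.1%, arises only if failures are recoded as negative. Under the plan's own exclusion, sensitivity power stays at 81–89% with 23 to 25 cases. This objection stands.

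**The classification rule does not already cover failures.** Its residual category can be read as sending them to negative, but it speaks of combinations of recorded readings, and an absent or void reading is not one. This stands.

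**Recoding is not neutral.** It slightly raises specificity, the prioritised measure. Some missing results may also reflect research logistics, since the sample is passed to a research team for testing. Counting those as device failures would be unfair to the device. Both points shape the fix.

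**Sensitivity analyses are planned, and the analysis plan is still to be finalised.** True, but they are qualified, no method is given, and they are aimed at model development and performance. The primary exclusion is already fixed, so this is not merely detail left for later. Requiring both control lines for the combined test is a legitimate stated choice; it is less apt for accuracy of one marker alone.

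**Conclusion.** The concern holds in a limited form. The primary analysis is restricted to participants with an LVOne result, the status of invalid tests is undefined, and 257 has no allowance for lost tests. Valid-only accuracy is a defensible quantity but not the same as rule-in performance in all tested patients, and the plan names no analysis that gives the latter.

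The power effect is modest. If 2% to 10% of results are lost and not replaced, exact power for specificity is about 75–79% instead of 81.6%; power for sensitivity remains above 80%. This rests on the assumed loss rates, on losses unrelated to diagnosis, on 10% prevalence, and on the exact two-sided test that reproduces 257. The documents establish neither an overstated sensitivity nor a certain shortfall in sample size.

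**What to change.** 1. **Define the handling and add a named analysis.** State that invalid tests are handled together with missing ones. Beside the valid-only result, report an all-tested analysis in which device failures count as not ruled in, with failure rates by final diagnosis and a note that this lowers sensitivity and slightly raises specificity. Keep results never obtained for research-logistics reasons separate from device failures.
2. **Model development.** Impute missing LVOne scores from the same-time ELISA values, clinical variables and outcome where the venous sample exists, with complete-case analysis as a sensitivity analysis. Where both samples failed, ELISA cannot help.
3. **Single-marker accuracy.** Judge validity per assay for GFAP alone and D-dimer alone.
4. **Sample size.** State that 257 and its 80% power refer to participants with an analysable LVOne result, and align the stopping rule and monitoring with that; otherwise restate the power for the expected loss.

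Items 1 to 3 need wording and analysis of data already being collected; the reason each result is missing must be recorded. Item 4 costs about 6, 14 or 29 extra participants at 2%, 5% or 10% loss (263, 271 or 286 less 257), or nothing if the lower power is accepted and stated. The all-tested sensitivity will look less favourable than the valid-only figure whenever a true case fails.

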### Sample size

This study aims to ‘rule in’ patients with ICH and LVO; therefore, the sample size calculation prioritises high specificity.

Assuming a 10% prevalence of both ICH and LVO, a sample size of 257 patients with suspected stroke is required, including a minimum of 26 confirmed cases for each subtype. The sample size calculation is based on a diagnostic accuracy framework using the method described by Bujang and Adnan,^24^ in which null and alternative hypotheses are specified for sensitivity and specificity.

Based on our previous work, which demonstrated a specificity of 90% and a sensitivity of 50% for a clinical model with nine predictors,^25^ the current study is powered to detect an improvement to 95% specificity and 80% sensitivity for the detection of ICH and LVO, with 80% power and a significance level of 0.05.^24^

The number of cases contributing to the primary analysis will be monitored throughout the study. If necessary, recruitment may be adjusted to ensure adequate representation of target subtypes.

## Monitoring and quality assurance

The study will be subject to internal monitoring led by the Chief Investigator to ensure it is conducted in accordance with the approved protocol, good clinical practice (GCP) and applicable regulatory standards. Routine monitoring activities may include a review of informed consent documentation, verification of source data and assessment of compliance with study procedures at participating sites.

## Safety considerations and adverse events

In this observational study, risks to participants are expected to be minimal. Research blood samples will be collected alongside routine clinical samples where possible. When this is not feasible, additional venous samples may be obtained following verbal consent. Finger-prick sampling for the LVOne test may cause minor discomfort or bruising; however, these effects are rare and transient. All procedures will be performed by trained clinical staff.

All events, including adverse events and serious adverse events, considered by the local team to be potentially related to the device will be recorded. Serious adverse device effects will be reported by the Chief Investigator or Principal Investigator within 24 hours to the study sponsor (The University of Manchester) and the host hospital research and development department.

## Peer review

Funding for the study was awarded through the Confidence for Translation (C4T) scheme at the University of Manchester, and the funding application was reviewed by six independent scientific experts at the University of Manchester. In addition, the protocol was reviewed by two expert stroke academics from other institutions, independent of the DIAGNOSIS study team.

